#### 596 **10.4. Assessment of Expectedness**

597 The RSI (US Prescribing Information, found in the Appendix A of the IMPD or here:  
598 [www.dailymed.nlm.nih.gov](http://www.dailymed.nlm.nih.gov)) lists all known expected events in relation to the administrations of the trial  
599 drug (EXPAREL) and the control (bupivacaine hydrochloride) during surgery (see section 10.2.1 above).

600 Assessment of expectedness will be performed against what is documented in the RSI and will be done  
601 centrally and independent of the site's PI.

602 If during the trial, a non-serious expected adverse reaction listed in the RSI is observed as serious then  
603 this will also be reported as a SUSAR. In addition, in the unlikely event that an adverse reaction is fatal or  
604 life-threatening this will also be reported as SUSAR.

#### 605 **10.5. SUSAR Reporting**

606 All SUSARs will be processed by the Oxford study office to the relevant Competent Authority, REC,  
607 Sponsor QA office and other parties as applicable. For fatal and life-threatening SUSARS, this will be done  
608 no later than 7 calendar days after the Sponsor or delegate is first aware of the reaction. Any additional  
609 relevant information will be reported within 8 calendar days of the initial report. All other SUSARs will be  
610 reported within 15 calendar days.

611 Principal Investigators will be informed of all SUSARs for the relevant IMP for all studies with the same  
612 Sponsor, whether or not the event occurred in the current trial.

#### 613 **10.6. Data Safety and Monitoring Committee & Trial Steering Committee**

614 A Data Safety and Monitoring Committee (DSMC) will be appointed to safeguard the interests of the trial  
615 participants, to assess the safety and efficacy of the interventions during the trial, and to monitor the  
616 overall conduct of the trial, protecting its validity and credibility. The DSMC will be independent of the  
617 trial investigators and sponsor, and will adopt a DAMOCLES charter that defines its terms of reference  
618 and operation in relation to oversight of the trial. It will meet at least every 12 months over the duration  
619 of the trial. The DSMC will not be asked to perform any formal interim analyses of effectiveness. It will,  
620 however, review accruing data and summaries of that data presented by the treatment group and will  
621 assess the screening algorithm against the eligibility criteria. It will also consider emerging evidence from

other related trials or research and review any related SAEs that have been reported. The DSMC may advise the chair of the Trial Steering Committee (TSC) at any time if, in its view, the trial should be stopped for ethical reasons, including concerns about participant safety or clear evidence of the effectiveness of one of the treatments. The DSMC will comprise of two independent medically qualified clinicians and a statistician.

In addition to a DSMC, a TSC will be appointed whose primary function is to act as an oversight body for the trial on behalf of the Sponsor and funding body. The TSC will be chaired by an independent member and will consider and act, as appropriate, upon the recommendations of the DSMC and ultimately carries the responsibility of deciding whether or not the trial needs to be stopped on the grounds of safety. The TSC will adopt a charter that defines its terms of reference and operation in relation to the oversight of the trial and will meet at least every 12 months over the duration of the study.

The Sponsor QA office will be provided with the trial committee charters and minutes.

## **10.7. Development Safety Update Reports**

Where appropriate, the trial management team will submit Development Safety Update Reports (DSURs). These will be submitted (in addition to the expedited reporting above) once a year throughout the clinical trial, or on request, to the Competent Authority (Medicines and Healthcare products Regulatory Agency (MHRA) in the UK), Ethics Committee, Host NHS Trust and Sponsor.

## **11. STATISTICS**

### **11.1. Description of Statistical Methods**

This section provides a brief summary of the statistical and cost effectiveness analysis with full details being included in separate stand-alone Statistical Analysis Plan (SAP) and Health Economic Analysis Plans (HEAP). These will be drafted early in the trial and finalised prior to the final datalock and any formal analysis of primary outcomes.

The primary objective of improved patient recovery will be assessed by analysing the two primary endpoints: global QoR-40 scores at 72 hours and cumulative pain score from 6 to 72 hours following surgery. The QoR-40 is a global measure of quality of recovery. It incorporates five dimensions of health: patient support, comfort, emotions, physical independence, and pain; each item is graded on a five-point Likert scale. QoR-40 scores range from 40 (extremely poor quality of recovery) to 200 (excellent quality of recovery) [32]. The null hypothesis that there is no difference between the treatment arms will be rejected if either of these outcomes are statistically different at the 2.5% significance level. The trial will be considered to have a positive result if either of the dual primary outcomes return a positive result.

Pain scores will be assessed daily in the evening at approximately 6, 24, 48 and 72 hours post-surgery, using a 0-10 VAS and cumulative pain scores will be calculated as area under the curve.

Both of the primary outcomes will be analysed using multivariate linear regression adjusting for stratification factors and other important prognostic variables, including baseline scores in the case of the QoR-40. The adjusted mean difference between the two groups together with 97.5% confidence intervals will be reported for each of the primary outcomes. If either of the primary outcomes is not

normally distributed, transformation to normality will be the first approach. If this is not possible, then non-parametric techniques without adjustment will be used.

As secondary analyses both pain and QoR-40 measured at 6, 24, 48 and 72 hours will be assessed using longitudinal methods to take account of the multiple-time points and the correlation between them. Multi-level, multivariate linear regression modelling with adjustment for the same factors as the primary analysis will be used. Other continuous variables will be analysed using similar methodology. For binary variables the number and percentage of patients in each category will be reported for each treatment group and overall. Chi-squared tests will be utilised for comparing the treatments, with additional analyses being undertaken using multi-variable logistic regression with adjustment for stratification and other important prognostic factors if sufficient events have been observed.

Reporting of the results will be based on the CONSORT statement.

It is anticipated that all statistical analysis will be undertaken using Stata (StataCorp LP, [www.stata.com](http://www.stata.com)) or other well-validated statistical packages.

Health Economic Analysis: A cost utility analysis will also be performed using quality-adjusted life years (QALYs) as the main health outcome, obtained using the EuroQol EQ5D-5L questionnaire at baseline, 72 hours, 6 weeks, 6 months and 1 year. The perspective of the analysis will be societal and costs will be informed by collecting data on the initial surgery, cost of treatment and analgesic medication, primary/hospital and social care resource use over the first year following surgery, out-of-pocket expenses (e.g. over the counter medications, travel costs to attend consultations, private practitioners, etc.), unpaid care from family members or friends and loss of earnings resulting from knee replacement. Such data will be collected from hospital medical records and using self-completed patient questionnaires at 6 weeks, 6 months and 12 months. Healthcare and social care utilisation will be valued using national databases [33, 34].

The results of the cost utility analysis will be presented using an incremental cost-effectiveness ratio expressed as cost per QALY gained and interpreted as the additional costs/savings associated to the additional QALY benefits of Liposomal bupivacaine compared to Bupivacaine hydrochloride.

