 123 (NSAIDs), cyclooxygenase-2 inhibitors, paracetamol, gabapentinoids, ketamine, and local and regional  
 124 anaesthetic techniques reduce the need for oral or parenteral opioids in the post-operative period, and  
 125 as a consequence their side effects, is reduced. Multiple studies report the superiority of multi-modal  
 126 analgesia over single agent therapy [2].

127 Local anaesthetic incisional infiltration is commonly used as part of a multi-modal technique with the  
 128 view that modification of pain stimuli at their origin will reduce the transmission of nociceptive stimuli,  
 129 thereby reducing downstream organ dysfunction, pain and stress responses, including centrally  
 130 mediated changes in the spinal cord or the cerebral cortex which all contribute to post-operative  
 131 morbidity and mortality. The half-life of local anaesthetics is dependent on the rate at which they  
 132 disassociate from voltage-gated sodium channels with bupivacaine being one of the longest acting local  
 133 anaesthetics with a half-life of 120 to 240 minutes [14]. Whilst the clearance and subsequent hepatic  
 134 metabolism of bupivacaine can be delayed by the addition of drugs such as epinephrine the length of  
 135 their duration of action is a major limiting factor of current local anaesthetic techniques and despite  
 136 multi-modal techniques a significant number of patients report severe post-operative pain following  
 137 knee replacement. Current methods to address this, including continuous short acting local anaesthetic  
 138 infusions, remain unsatisfactory due to the increased risk of infection, interference with early  
 139 mobilization and discharge caused by the use of an indwelling infiltration catheter as well as additional  
 140 cost of infusion devices. Due to the inherent benefits of targeting peripheral receptors a great deal of  
 141 interest has been invested in developing long acting local anaesthetics such as liposomal bupivacaine.

Liposomal bupivacaine (EXPAREL, Pacira Pharmaceuticals Inc., San Diego, California 92121) is liposome encapsulated bupivacaine which has been reported to be effective for up to 72 hours [15, 16]. Using a proprietary technique known as DepoFoam (SkyePharma, London, UK) the local anaesthetic bupivacaine is held within multi-vesicular liposomes which permit prolonged release through diffusion, membrane breakdown and re-organisation [17].

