## 6.3. Patient Participation

Patients will be involved for a maximum of 12 months post-randomisation. Post operatively, patients will be asked to complete Quality of Recovery-40 assessment daily and a visual analogue scale (VAS) pain score 0-10 on the evening of surgery (day 0) and on days 1, 2 and 3 following surgery. The analgesia requirements of each patient will be recorded. The time of surgery for the patient will be noted. The day of surgery will be called Day 0.

If the patients are discharged home prior to 72 hours postoperatively, then a phone call will be made daily to the patient to collect pain VAS and QoR-40. Pain VAS will be collected by asking the question 'How painful has your operated knee been over the past 24 hours on a scale of 0-10?' The EQ-5D-5L section of the questionnaire will also be completed over the telephone if deemed appropriate. If the patient cannot be contacted between those hours, then an additional call will be made between 2pm and 6pm and this will be noted.

Fitness for discharge will be assessed as per routine clinical care on the evening of surgery (day 0) day 1, 2 and 3 following surgery, until the patient is deemed fit for discharge. This is assessed against the following criteria:

- Ability to mobilize independently
- Pain score less than or equal to 3cm on a 10cm VAS

- Ability to straight leg raise
- Ability to bend knee to 90 degrees

Once discharged, patients will be assessed as per routine clinical care. The Central Study Office will post questionnaires to patients for completion at 6 weeks post-surgery, and at 6 months and 1 year following randomisation. The local hospital research team should encourage timely completion of questionnaires if these time points coincide with the routine follow up appointments. Assessments will include completing the Quality of Recovery 40, Oxford Knee Score, American Knee Society Score and EQ-5D-5L. In addition, an analgesic history will be taken.

A trial flowchart is provided in appendix A.

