#### 8.4. Baseline Assessments

Prior to randomisation the following information will be collected:

- Patient demographics (gender, age at surgery, body mass index)
- Summary medical history
- Summary medication history (current medication and duration of current medication, changes to current medication in the last 6 months, any history of prior opiate use)
- Quality of Recovery 40
- Pain Visual Analogue Scale (0-10) at rest
- Oxford Knee Score
- Clinical Assessment - American Knee Society Score
- Patient expectations of treatment
- Summary healthcare and social services use as well as informal care in the past 6 months due to knee (GP visits, outpatient visits, allied healthcare contacts, hospital admissions, medications, meals on wheels, and unpaid care)
- Summary employment history (in paid employment, not in employment, time away from work or usual activities)
- EuroQol EQ-5D-5L

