#### 8.5. Subsequent Assessments & Visits

Following surgery (day 0) and the 3 days following (days 1, 2 and 3) in the evening, the following information will be collected:

- Quality of Recovery 40
- Pain Visual Analogue Scale (0-10) at rest
- Cumulative opiate use (refer to patient medical notes)
- EuroQol EQ-5D-5L

Routine clinical assessments will also occur at the in-patient stage, including assessment of fitness to discharge. This information will be recorded for trial purposes.

Once discharged, patients will be seen again as per local routine clinical care. The Central Study Office will post questionnaires to patients for completion at 6 weeks post-surgery, and at 6 months and 1 year following randomisation. The following information will be collected:

- Summary medication history (since last assessment)
- Quality of Recovery 40
- Pain Visual Analogue Scale (0-10) at rest
- Oxford Knee Score
- Clinical Assessment - American Knee Society Score
- Summary healthcare and social services use as well informal care in past period due to knee (GP visits, outpatient visits, allied healthcare contacts, hospital admissions, medications, meals on wheels, and unpaid care)
- Summary employment history (in paid employment, not in employment, time away from work or usual activities)
- EuroQol EQ-5D-5L

If the patient does not return the postal questionnaire within 7 days, another questionnaire will be posted as a reminder. Following this, if we have not received a completed questionnaire within 14 days, all patient reported data will be recorded over the telephone.

An assessment table is provided in Appendix B.

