Oxford Knee Score (OKS) – a 12-item patient-reported outcome measure designed to measure pain and function after knee replacement surgery [20]. Each question is scored from 0 (worst outcome) to 4 (best outcome). A total score is obtained by summing across all 12 items to give a single score with a range from 0 (worst outcome) to 48 (best outcome). This outcome will be assessed at 6 weeks, 6 and 12 months post-randomisation.

American Knee Society Score – patient reported outcomes from the AKSS will be collected at baseline, 6 weeks, 6 months and 1 year post-surgery. The AKSS is split into categories where patients record details of satisfaction with treated knee, expectations from their surgery, and ability to perform functional activities. Total scores will be calculated using the scoring manual [21]. The patient satisfaction score composes 5 questions with a maximum score of 40. The patient expectation score composes 3 questions with a maximum score of 15. The functional score is composed of 4 subgroups (walking and standing; standard activities; advanced activities and discretionary activities) with a maximum score of 100. Higher scores indicate better performance. This outcome will be assessed at 6 weeks, 6 and 12 months post-randomisation.

EQ-5D – a validated measure of health-related quality of life consisting of a five dimension health status classification system with 5 response levels (EQ-5D-5L) and a separate visual analogue scale [22, 23]. Responses to the health status classification system will be converted to multi-attribute utility scores, scaled such that 1 is equivalent to perfect health, 0 is equivalent to death, and scores worse than death are possible. The UK value set will be used to generate the EQ-5D-5L index. This outcome will be assessed at 72 hours following surgery, 6 weeks, 6 months and 1 year post-randomisation.

Summary healthcare, social services use and employment history – will be summarised and analysed by the trial health economist. A separate health economics analysis plan will be prepared.

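### The named QALY readings omit the EQ-5D-5L collected on days 0, 1 and 2 and leave a 39-day gap after 72 hours, with no stated interpolation rule

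*Combined protocol and SAP*

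**What the plan says.** Protocol 11.1 and SAP 6.8 give the same list for the cost-utility analysis: utility "obtained using the EuroQol EQ5D-5L questionnaire at baseline, 72 hours, 6 weeks, 6 months and 1 year". The objectives tables in both documents agree. SAP 6.1 defines the EQ-5D outcome without days 0 to 2: "This outcome will be assessed at 72 hours following surgery, 6 weeks, 6 months and 1 year post-randomisation".

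The collection schedule is fuller. EQ-5D-5L is among the items that protocol 8.5 lists under "Following surgery (day 0) and the 3 days following (days 1, 2 and 3) in the evening", and Appendix B ticks it at baseline, days 0, 1, 2 and 3, 6 weeks, 6 months and 1 year. Nothing falls between day 3 and 6 weeks. Baseline is pre-drug: "Prior to randomisation the following information will be collected" (protocol 8.4). For patients sent home before 72 hours, protocol 6.3 says: "The EQ-5D-5L section of the questionnaire will also be completed over the telephone if deemed appropriate".

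The protocol's background section describes the drug as "reported to be effective for up to 72 hours". Neither document states how utilities are joined between readings. Both call for a separate HEAP, which is not part of what was reviewed.

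**The concern.** The intervention is a single intra-operative dose whose reported analgesic action lies within the first three days. For pain, the trial integrates readings at about 6, 24, 48 and 72 hours. For utility, readings on the same days exist, but the QALY list keeps only the last of them. The next reading is about six weeks after surgery.

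With so few points, the QALY difference depends on what is assumed between them. An early benefit that has gone by 72 hours may not register. A benefit seen at 72 hours may be spread over weeks in which nobody measured it. Cost-effectiveness is in the trial's title and is a stated secondary objective, so the cost per QALY could turn on an assumption that neither document states or tests.

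A related weakness is that the 72-hour value carries much of the weight, yet for patients already home it is asked by telephone only at staff discretion.

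**Working it through.** The documents give no QALY figure, utility difference or cost-effectiveness ratio, so there is no stated result to reproduce. The check compares the area that the listed readings would credit with the area under several assumed shapes of effect.

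**Inputs from the documents**
- Listed QALY readings: days 0 (baseline), 3, 42, 182.5 and 365.
- Collected but not listed: the evenings of days 0, 1 and 2. The day 0 reading is placed at day 0.25, about 6 hours.
- Gap after 72 hours: 42 − 3 = 39 days. Appendix B allows the 6-week form ±2 weeks (day 28 to 56), so the gap can be 25 to 53 days.
- Drug price, for scale only: 300 USD per patient (protocol section 4).

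**Assumptions**
- Straight-line interpolation between readings.
- A between-arm utility difference d, which is zero at baseline. The documents give no value, so a range of 0.02 to 0.30 is shown.

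**Formula.** Credited area = sum of (mean of adjacent differences × days between them). Divide by 365 for QALYs.

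For a difference d that lasts to 72 hours and then ends:
- Area under this shape: 3d days.
- Listed readings: (3 × d)/2 + (39 × d)/2 = 1.5d + 19.5d = 21d days.
- Ratio: 21/3 = 7. The share credited after 72 hours is 19.5/21 = 93%.
- With the 6-week form at day 28: 1.5d + 12.5d = 14d. At day 56: 1.5d + 26.5d = 28d.

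The same calculation for other shapes, in units of d-days (ratio to the area under the shape in brackets):

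| Assumed shape of the difference | Area under shape | Listed readings | Listed plus days 0, 1, 2 |
|---|---|---|---|
| d to 72 h, then nil | 3.0 | 21.0 (7.0) | 22.375 (7.5) |
| d to 72 h, linear to nil at day 7 | 5.0 | 21.0 (4.2) | 22.375 (4.5) |
| d to 72 h, linear to nil at day 42 | 22.5 | 21.0 (0.93) | 22.375 (0.99) |
| d to 48 h, then nil | 2.0 | 0 | 2.375 (1.19) |
| linear from d to nil at 72 h | 1.5 | 0 | 1.375 (0.92) |

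The early readings correct the last two rows but leave the first two slightly worse, because that error lies wholly in the day 3 to day 42 leg. The 0.93 assumes the 6-week form is completed at day 42.

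**In QALYs.** For d = 0.10 in the first row: 3 × 0.10/365 = 0.0008 against 21 × 0.10/365 = 0.0058. For d from 0.02 to 0.30: 0.00016 to 0.0025 against 0.0012 to 0.0173. The ratio is 7 throughout.

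**Effect of the assumption on the 39-day leg**, using all collected readings. The area to day 3 is 0.125d + 2.75d = 2.875d. Add the triangle after day 3:
- Ends by day 7: 2.875d + 2d = 4.875d.
- Ends by day 14: 2.875d + 5.5d = 8.375d.
- Runs to day 42: 2.875d + 19.5d = 22.375d.

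At d = 0.10 these are 0.0013, 0.0023 and 0.0061 QALY. With the 300 USD price and no other costs, that is about 225,000, 131,000 and 49,000 USD per QALY. These show only how far the result can move; they are not estimates.

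**The case against.** Protocol 11.1 describes itself as a brief summary and sends the detail to the HEAP, and SAP 6.8 says that the statistician does not do this analysis. The interpolation rule, any use of days 0 to 2, and the handling of missing utilities may all be there. This stands: what the two documents show is an incomplete list of time points and an unstated rule, not a wrong QALY. It does not remove the point, because the list is fixed in both documents and the HEAP would be written against it.

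A reader might infer that the QALYs miss the drug's period of action altogether. They do not: the 72-hour reading lies at the end of that period and is used, so a difference still present then is half counted before 72 hours (1.5 of 3 d-days). The period is missed entirely only if the difference has gone by 72 hours.

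A reader might also take the factor of 7 as a demonstrated bias. It needs straight lines and a full effect that stops just after 72 hours. The 72-hour figure describes the local anaesthetic, not quality of life. Protocol section 4 argues that poor early pain control delays mobilisation and worsens long-term function, so later benefit is part of the hypothesis. If benefit fades over six weeks, the listed readings are nearly right.

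The costs are equally open. The analysis is societal, and protocol section 4 cites a reported saving of 420 USD per case, which exceeds the drug price and could reverse the sign.

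On the telephone clause, protocol section 4 gives an average stay of 3 to 6 days, so many patients may still be inpatients at 72 hours. Selective loss among early leavers is possible, but its size cannot be estimated from the documents.

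**Conclusion.** The point holds as a gap in specification. Readings that the trial already schedules on days 0, 1 and 2 are left out of the named QALY list without a reason, and the 39 days after day 3 have neither a reading nor a stated rule. Under the assumed straight lines, the consequence runs in both directions: zero credit for a difference that has gone by 72 hours, and credit ranging from about right (0.93) to 7 times too large for one still present then. The data cannot show which case applies, because nothing is measured between day 3 and 6 weeks; that is why a sensitivity analysis is needed.

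No particular bias, cost per QALY or changed decision has been shown, since d and the cost offsets are unknown. The co-primary endpoints are unaffected; this concerns the secondary cost-utility analysis only.

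**What to change.** 1. In protocol 11.1, SAP 6.8 and the HEAP, compute QALYs from every collected EQ-5D-5L reading: baseline, days 0, 1, 2 and 3, 6 weeks, 6 months and 1 year. Hold the baseline utility to the day of surgery. This corrects the under-counting before 72 hours. It does not touch the 39-day leg.
2. For that leg, state the interpolation rule and pre-specify a sensitivity analysis in which the day-3 difference ends before 6 weeks, for example by day 7 and by day 14. Those two days are illustrative; the documents give no basis for a particular choice.
3. In protocol 6.3, remove the discretionary qualifier on telephone EQ-5D-5L, so that it is always asked at the daily call up to 72 hours. This helps only patients still to be assessed.

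Items 1 and 2 need no new data and can be settled before the HEAP is finalised, which protocol 11.1 places before data lock. The cost is a little more analysis and, for item 3, a few more minutes per call.
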